### Outcomes and endpoints

Our primary outcome is the acute respiratory exacerbation rate by 12 months postrandomisation. These are collected by participant reports (active surveillance of participants) and medical records.

In children, we will use the definition used previously^18 43^ that is also in accordance with the ERS-based guidelines^2^ and the ERS Task Force international consensus definition of an exacerbation.^3^ For children, an episode is defined by an acute respiratory event that (1) is treated with antibiotics and (2) has an increase in sputum volume and/or purulence, or >3 days of change in cough (at least 20% increase in cough score or change in quality (dry to wet/productive)) or physician-confirmed acute change in respiratory rate, effort or chest signs.^3^ For adults (aged>18 years), we will use the adult consensus definition that is, a clinician determines that treatment change is required and deterioration in ≥3 of the following for ≥48 hours (cough, sputum volume or purulence, breathlessness, exercise tolerance, fatigue and/or malaise, haemoptysis).^24^

Other outcomes (see online supplemental material for further information) are as follows:

10.1136/bmjresp-2023-002216.supp1Supplementary data

QoL scores at 12 months: In adults, we are using the bronchiectasis QoL tool (B-QoL),^44^ which has 37 questions with a respiratory subdomain score. In the absence of a bronchiectasis-specific QoL for children, we are using the validated Parent-proxy Cough QoL-8 instrument (PC-QoL).^45^
Time-to-next exacerbation: Defined from the time of commencing trial medications to the next respiratory exacerbation (defined above), measured in days.Time-to-next respiratory-related hospitalisation.Spirometry values (forced expiratory volume in 1 s (FEV_1_ z-score) and forced vital capacity (FVC) z-score, and FEV_1_/FVC ratios).Adverse events, including gastrointestinal symptoms (eg, nausea, vomiting, abdominal pain, diarrhoea), headaches, rashes, use of additional non-macrolide antibiotics for non-pulmonary infections during the intervention, that is, for 12 months postrandomisation.Healthcare resource use.

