The pathobiology of bronchiectasis includes the coexistence of chronic lower airway infection and inflammation, mucus hypersecretion and disruption of mucociliary clearance, which are all integral to the vicious vortex (previously labelled the vicious cycle) hypothesis of bronchiectasis,^7 20^ and are also thought to operate in people with COPD.^21^ Clinically these processes result in wet/productive cough, symptoms that are particularly bothersome for people with bronchiectasis.^14^

Recurrent respiratory exacerbations are also a characteristic feature of broncheictasis.^20 22^ Reducing exacerbations is important as these episodes impair quality of life (QoL) and can lead to an accelerated decline in lung function and high utilisation of healthcare resources.^20 22–24^ A prospective multicentre study involving 85 children with bronchiectasis found that the mean number of exacerbations was 3.3 (SD 2.2) per child-year.^25^ In any given month, 25% of these children were absent from school/childcare, 30% attended a healthcare appointment and 46% received antibiotics due to bronchiectasis while 11.4% of respiratory exacerbations required hospitalisation.^25^

Interventions that might reduce respiratory exacerbations and sputum volume would be beneficial to people with bronchiectasis as these factors are considered by clinicians and patients as the most challenging aspects of managing bronchiectasis.^13 14^ Mucoactive agents, such as erdosteine, are one such intervention that could address both of these patient and clinician priorities.^26–28^

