The coexistence or overlap of COPD with bronchiectasis has long been recognised. A meta-analysis of 18 studies found that the prevalence of bronchiectasis in COPD was 54% (range 25%–69%).^37^ Another meta-analysis of 14 observational studies described comorbid bronchiectasis in COPD with increased the risk of exacerbation (1.97, 95% CI 1.29 to 3.00), severe airway obstruction (1.31, 95% CI 1.09 to 1.58) and mortality (1.96, 95% CI 1.04 to 3.70).^38^ This meta-analysis also reported a wide range of coexistent bronchiectasis from 4% to 72%.^38^ Consequently, studies involving erdosteine in adults with COPD are also relevant in informing the rationale for our study.

In adults with COPD, a systematic review of interventions for preventing respiratory exacerbations included two RCTs using erdosteine.^27^ Both RCTs (8–12 months duration) found that erdosteine significantly reduced hospitalisation, antibiotic use and respiratory exacerbations and improved QoL and lung function.^27^ A meta-analysis^28^ of individual patient data (n=1046) on erdosteine also found it was associated with significant symptom amelioration, compared with either placebo or other mucoactive agents in patients with chronic bronchitis/COPD. A network meta-analysis^39^ (seven RCTs) found that erdosteine was superior to other mucoactive agents (eg, carbocysteine) for reducing acute COPD respiratory exacerbations and hospitalisation. A more recent post hoc RCT analysis of adults with moderate-to-severe COPD also described clinical benefits when erdosteine was added to their usual maintenance therapy for a 12-month period (compared with placebo).^40^ The improved clinical outcomes included improved QoL and patient-reported disease severity and reduction in proportion of patients who had exacerbations requiring antibiotics and/or corticosteroids (74.3% vs 80.8%, p<0.05).^40^

Thus, erdosteine is a promising novel mucoactive that may be beneficial for people with bronchiectasis. It is possible, but unknown, if prolonged treatment for 12 months will benefit children and young adults with bronchiectasis. As these actions target part of the underlying pathobiological mechanisms in people with bronchiectasis, it is plausible that regular erdosteine could improve clinical outcomes.

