## Methods and analysis

### Design

We are undertaking a parallel, double-blind, placebo, superiority multicentre RCT (with concealed allocation) to determine the efficacy of 12 months of erdosteine at reducing acute respiratory exacerbations and improving other clinical outcomes. We randomised the first participant in May 2021 and we anticipate continuing recruitment until at least July 2024. This RCT started recruiting concurrently with our other RCT that also involved erdosteine in one of its arms, where the goal was to reduce exacerbations in people with primary ciliary dyskinesia.^41^ Thus, these RCTs have many shared methods and descriptions of data collected.

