#### Data and sample collection, monitoring and follow-up details

All collected data are recorded by GCP-trained researchers using standardised data sheets or online surveys (similar to our previous RCTs).^18 19 42^

At enrolment, sociodemographic/clinical data, spirometry (in those aged >6 years) and specimens (sputum and blood where possible in a subset of participants contributing to the discovery component) are collected (table 1).

**Table 1 T1:** Schedule for visits and contact points

Visit type	Baseline	Month												
		1	2	3	4	5	6	7	8	9	10	11	12	Start of exacerbation (if possible)
Screening for eligibility	√													
Informed consent (paper or electronic)	√													
Randomisation	√													
Medical history	√													
Medical chart review	√			√			√			√			√	
Monthly parent/participant contact recording exacerbations		√	√	√	√	√	√	√	√	√	√	√	√	
Clinical assessment (where possible)	√			√			√			√			√	√
PC-QoL-and/or QoL-B questionnaire	√						√						√	√
Spirometry (if possible)	√			√			√			√			√	√
Urine pregnancy test (only females ≥14 years	√						√						√	
Study diary	√						√						√	√
Blood in subgroup	√													√
Sputum in subgroup	√													

B-QoL, bronchiectasis QoL tool; PC-QoL, Parent-proxy Cough QoL-8 instrument; QoL, quality of life.

Sociodemographic data include details of age, gender, family and household size, cigarette smoking, family and immunisation history, medications and comorbidities. These are obtained from the carers/participants and/or reviewing the medical notes. Participants are contacted every month via electronic communication (email or short-message service texting) or by telephone to monitor progress and adverse events (eg, vomiting, diarrhoea, rash) and economic data (eg, medical visits, treatments, other interventions, school/work absenteeism). Participants are seen in the clinic 3–4 monthly as part of their routine clinical care (if they reside locally at one of the study sites) and at the onset of their first exacerbation following enrolment where additional clinical data and biological specimens are collected (table 1), if possible. Specimens will be stored and analysed later. We have established robust methods for capturing respiratory exacerbations.^18 19 43^ Hospital records are also reviewed for hospitalisations. Additionally, at enrolment, a pregnancy test is undertaken if a female participant is aged ≥14 years.

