#### For the primary aim

To assess erdosteine efficacy, the exacerbation rate in those randomised to receive erdosteine will be compared with controls (receiving placebo). We will use a negative binomial regression model (as recommended,^46^ including treatment group, and number of months in the study included as an offset) to determine between-group differences (with 95% CI), as done previously.^19^

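### The adverse-event item on antibiotic use leaves out macrolide courses for non-pulmonary infections, for no stated reason, although neither arm gives a macrolide

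*Protocol article*

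**What the plan says.** The Outcomes and endpoints section lists a safety outcome that opens "Adverse events, including gastrointestinal symptoms" and goes on to headaches, rashes and "use of additional non-macrolide antibiotics for non-pulmonary infections during the intervention, that is, for 12 months postrandomisation". The antibiotic item therefore has two limits: by drug class and by indication.

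The trial has two arms. Under the primary aim, "the exacerbation rate in those randomised to receive erdosteine will be compared with controls (receiving placebo"; the Trial medications section describes only erdosteine and its matching placebo.

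Antibiotics also appear in three other places:

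- **Primary outcome.** For children, "an episode is defined by an acute respiratory event that (1) is treated with antibiotics" and also meets a symptom or sign criterion. For adults, a clinician must judge that treatment has to change, and at least three listed symptoms must have worsened for 48 hours or more.
- **Monthly contact.** The data collection section records "economic data (eg, medical visits, treatments, other interventions, school/work absenteeism", with no limit by drug class or indication.
- **Healthcare resource use.** This is a listed outcome, summarised by arm for the cost-effectiveness work.

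**The concern.** A limit by drug class in an outcome needs a reason in the design. If a macrolide were a study drug, separating macrolide from non-macrolide courses would make sense. Here no arm gives one, and the article does not say what the limit is for.

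Whether a treated infection enters the item then depends on which antibiotic the prescriber chose, not on whether the participant had an infection that needed treatment. Other bronchiectasis care follows local practice (Study protocol), the sites lie in three countries (Study sites), and macrolide users are not excluded (Exclusion criteria). Prescribing choice can therefore vary.

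What is at stake is the completeness of one safety item, together with a clear account of where the remaining antibiotic courses are reported.

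**Working it through.** The article gives no figure for this item, so there is none to reproduce. The check sorts antibiotic courses by class and indication and asks which named clinical outcome would contain each.

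| Course | Named clinical outcome that contains it |
|---|---|
| Non-macrolide, non-pulmonary infection | Adverse-event item |
| Macrolide, non-pulmonary infection | None: removed by the class limit |
| Any class, qualifying exacerbation | Primary outcome; also time-to-next exacerbation if it is the first event |
| Any class, respiratory episode below the exacerbation definition | None, unless it leads to a respiratory hospitalisation |
| Long-term macrolide started during the trial as background care | None |

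**Row 2.** This is the only row in which the class limit decides the answer. One possible purpose is to set aside maintenance macrolides. However, the Introduction describes long-term macrolides as given to reduce acute exacerbations, which is a pulmonary purpose, so the restriction to non-pulmonary infections already removes them. What the class limit then removes in addition is macrolide treatment of non-pulmonary infections.

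**Row 3.** The child definition requires antibiotic treatment of any class, and the adult definition requires only a treatment change. A macrolide given for a qualifying exacerbation is counted in both.

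**Row 4.** Two examples follow from the definitions. The first is a treated child whose cough change settles within 3 days, with no change in sputum and no physician-confirmed sign. The second is a treated adult with only two of the listed symptoms. Neither has a qualifying exacerbation, and neither has a non-pulmonary infection.

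**Size.** Let *m* be the share of additional non-pulmonary courses that are macrolides. The item records a fraction 1 − *m* of them, so the undercount is *m*. The article does not give *m*.

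**Effect on the comparison.** With true rates R_E (erdosteine) and R_P (placebo) and the same *m* in both arms, the observed ratio is (1 − *m*)R_E / [(1 − *m*)R_P] = R_E / R_P. Absolute counts fall; the ratio does not change. Allocation is blinded and stratified by site, and nothing in the article suggests that *m* would differ by arm.

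**The case against.** The case against making much of this is strong, and most of it stands.

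- **The item is a safety entry.** It is one entry in an open adverse-events list, and antibiotic use is not among the stated aims. The Introduction's report that "erdosteine significantly reduced hospitalisation, antibiotic use and respiratory exacerbations and improved QoL and lung function" is background from COPD trials. A reader might infer that the plan has an antibiotic-use efficacy outcome that fails at its task; the article sets no such outcome.
- **The data may exist.** Treatments are recorded monthly, and resource use is summarised by arm. This stands as to collection. However, the article's Summary says that the economic evaluation will be reported later, outside the primary trial analysis, so it does not complete the safety item.
- **The supplement may say more.** The outcomes section refers to supplementary material that is not shown. That could supply a reason, but the restriction is stated in the article itself and is not a detail left out.
- **Every exacerbation definition excludes some treated episodes.** This is true, and the definitions follow published consensus. The uncounted respiratory episodes are a reporting gap, not a fault in the primary outcome.
- **The origin of the wording is unknown.** The Design section says of this trial and a sister trial: "Thus, these RCTs have many shared methods and descriptions of data collected". A reader might infer that the phrase was carried over from a trial with a macrolide arm. The article says only that the sister trial has erdosteine in one of its arms, so the inference is not established.

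**Conclusion.** The point holds as a minor one. The class limit is unexplained in an erdosteine–placebo trial and, read literally, drops macrolide courses for non-pulmonary infections from a safety item that counts other antibiotics for the same infections. Treated respiratory episodes below the exacerbation definition also have no named clinical outcome, apart from those that lead to a respiratory hospitalisation. The primary outcome, the power and the between-arm comparison are not affected.

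Two stronger readings are tempting and not supported. The first is that macrolide courses appear in no clinical outcome at all; those given for qualifying exacerbations do.

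The second is a numerical one. The Introduction reports a cohort of children in whom, in any given month, "30% attended a healthcare appointment and 46% received antibiotics due to bronchiectasis". One could compute 0.46 × 12 = 5.52 antibiotic-months per child-year, subtract 3.3 exacerbations, and call the remaining 2.22 (40% of 5.52) uncounted. That subtracts events from months of receipt. A course can span two months, and the 46% may include long-term treatment. It also concerns antibiotics for bronchiectasis and so says nothing about non-pulmonary courses. No size can be derived from these figures.

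The verdict assumes that the supplement does not redefine the item and that macrolide choice does not differ by blinded arm.

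**What to change.** Delete *non-macrolide*, so that the item covers all additional antibiotic courses for non-pulmonary infections over the 12 months. If the limit was intended, state its reason instead.

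Using the treatments already recorded at monthly contact, tabulate antibiotic courses by arm and by indication: exacerbation, other respiratory, non-respiratory. This shows where every course is reported, including respiratory episodes below the exacerbation definition.

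The cost is one wording change, an indication code, and some recoding for participants already enrolled. Rate-ratio models for antibiotic courses, or a sensitivity analysis of the primary outcome on antibiotic-treated respiratory episodes, would be optional additions; the point does not depend on them.

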### Data monitoring, management and analyses

All identifiable information on study participants will be retained in password-protected files stored on the QUT server or locked cabinets/rooms at study sites. Access to this information will only be provided to immediate study staff unless required by legislative or regulatory agencies and the HRECs. The principal investigator and statisticians will have access to the final trial dataset.

All adverse events, including serious adverse events, are monitored by an iDMC, which was established prior to commencing the study. An Indigenous (First Nations) Reference Group based at the Menzies School of Health Research (Darwin) oversees the cultural aspects of the study. Data coding and entry are coordinated in Brisbane and conducted in accordance with GCP.

The analyses will be directed by biostatisticians ([name] and [name]). Results will be reported and presented in accordance with Consolidated Standards of Reporting Trials guidelines. We will use the ‘intention-to-treat’ approach for the main analyses. We also plan a ‘per-protocol’ analysis. Missing data will not be imputed. No interim analysis is planned. A detailed statistical analysis plan will be developed and approved by the chief investigators and the iDMC before undertaking the final analysis. Any exploratory, post hoc or unplanned analysis will be identified clearly. Analysis code will be written and agreed on knowledge of treatment allocation and adherence is provided to the statistician, as done previously.^18 43^

#### For the primary aim

To assess erdosteine efficacy, the exacerbation rate in those randomised to receive erdosteine will be compared with controls (receiving placebo). We will use a negative binomial regression model (as recommended,^46^ including treatment group, and number of months in the study included as an offset) to determine between-group differences (with 95% CI), as done previously.^19^

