#### Sample size

Based on the primary outcome (exacerbation rate), we want to detect a significant difference between those allocated to erdosteine vs placebo (controls). We will use a negative binomial model (similar to our previous RCT),^19^ and we will have 90% power (alpha=0.05) to detect a 40% reduction in the respiratory exacerbation rate in the erdosteine group (controls=3/year, intervention=1.8/year), if we obtain final endpoint data from 164 persons. To account for a 25% attrition loss, we will enrol a total of 194 people. We conservatively estimated a 40% reduction in respiratory exacerbation rate based on the following: a paediatric study (total n=158) reported an absolute reduction in cough by 47% in those receiving erdosteine^32^ while adults with COPD allocated erdosteine (total n=155) had 58% fewer days in hospital,^27^ compared with placebo.

We postulate superiority between groups for QoL. The minimal clinical important difference for the PC-QoL instrument is 0.9^45^ (SD 1.8) while that of the adult B-QoL tool is domain dependent (7–10) (SD 17).^44^ With the standardisation of the scales, we will have 90% power to detect a difference of means between groups of 0.5 SDs. We are aware our study is insufficiently powered for the other secondary outcomes.

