### Impact of the SARS-CoV-2 pandemic on the clinical trial

The recent SARS-CoV-2 pandemic affected several aspects of our RCT. First, in 2021–2022, our recruitment was severely affected by strict state and regional lockdowns and travel restrictions preventing face-to-face visits required by our study. Also, the reluctance of parents/patients to attend clinics during the pandemic prevented effective recruitment. However, recruitment recovered as restrictions were eased. Second, the incidence of exacerbations over this period was substantially lower than that predicted, a phenomenon found worldwide coincident with the public health measures enacted to reduce transmission of SARS-CoV-2.^55 56^ Third, there are also financial consequences as no additional funds were made available by the funding body and research team members continued to be paid throughout this pandemic.

To address these challenges, we initiated several mitigations steps that included (1) using e-consents (approved by all ethics committees); (2) posting trial medications to the participant’s home (instead of participants collecting trial medications from hospital pharmacies) and (3) undertaking online (telehealth) follow-up where possible and appropriate. Nevertheless, we are uncertain whether our study’s findings will be adversely impacted by the SARS-CoV-2 pandemic.

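### The primary model has no calendar-period term although the article reports a substantial pandemic fall in exacerbations; one prespecified covariate would recover a modest amount of precision

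*Protocol article*

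**What the plan says.** The section on the primary aim specifies a negative binomial regression "including treatment group, and number of months in the study included as an offset". No other term is listed.

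The section on the impact of the pandemic places lockdowns and travel restrictions in 2021–2022 and states that "the incidence of exacerbations over this period was substantially lower than that predicted". Its responses are operational: electronic consent, posted medication and telehealth follow-up. The Design section gives first randomisation in May 2021 and recruitment until at least July 2024.

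The limitations section accepts that the trial may be underpowered for the primary outcome because of the pandemic. The only extra covariate it mentions is age, in a sensitivity analysis. Calendar period appears in no analysis. The data monitoring and analysis section defers a detailed statistical analysis plan to a later date, before the final analysis.

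The Sample size section assumes yearly rates of 3 on placebo and 1.8 on erdosteine. Its power statement is conditional: the stated power applies "if we obtain final endpoint data from 164 persons".

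**The concern.** The article names a predictor of its own primary outcome, says that predictor threatens power, and then writes a primary model that ignores it. With only treatment and a log-time offset, a month under restrictions and a month after them count as the same exposure. A participant followed mainly under restrictions is expected to have fewer exacerbations than one followed later. The model can place that difference only in the dispersion parameter, which enlarges the standard error of the log rate ratio.

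What is at stake is precision in a trial that already doubts its power. The dates needed to remove this variation are recorded at randomisation.

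**Working it through.** **Inputs from the article.** Rates 3.0 and 1.8 per year (rate ratio 0.60), 90% power, alpha 0.05, 164 with endpoint data, 12-month follow-up, entry from May 2021.

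**Assumptions not in the article.** Two-sided alpha; 1:1 allocation (82 per arm); the dispersion; the share randomised in the low period (20–50%); the fall in rate (30–60%); the end of the low period (mid- or end-2022); entry uniform on each side of that date; the same rate ratio in both periods.

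**Step 1: the plan's own figure.** For one year of follow-up, var(log RR) = (1/r0 + 1/r1 + 2k)/n per arm. The dispersion k is not stated, so 164 cannot be checked independently, but k can be solved for:
- (1.960 + 1.282)² = 10.507; ln(0.6)² = 0.2609
- 82 × 0.2609 / 10.507 = 2.036
- k = (2.036 − 1/3 − 1/1.8)/2 = 0.574

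A one-sided alpha would need k = 0.805.

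**Step 2: what pooling does.** Let m be a participant's expected rate relative to plan. Without a period term, the dispersion becomes k* = (1 + k)·E[m²]/E[m]² − 1, and the variance is (0.889/E[m] + 2k*)/82, where 0.889 = 1/3 + 1/1.8. With a covariate that captures m, the information is 82 × the average of 1/(0.889/m + 2k).

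**Step 3: upper bound, each participant wholly in one period.** Take 40% at half the rate. E[m] = 0.80, E[m²] = 0.70, k* = 0.721. Power is 82.5% without the term and 86.0% with it.

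**Step 4: follow-up allowed to straddle.** Again 40% randomised in the low period at half the rate, with the period ending in December 2022, 20 months after first entry. Let p be the share of a participant's 12 months in the low period.
- Of those randomised in the low period, the first 8/20 have p = 1. The other 12/20 have p uniform from 0 to 1. Mean p = 0.4 + 0.6/2 = 0.70; mean p² = 0.4 + 0.6/3 = 0.60.
- Over all participants, E[p] = 0.4 × 0.70 = 0.28 and E[p²] = 0.4 × 0.60 = 0.24.
- m = 1 − 0.5p, so E[m] = 0.86 and E[m²] = 1 − 0.28 + 0.25 × 0.24 = 0.78.
- k* = 1.574 × 0.78/0.86² − 1 = 0.660.
- Unadjusted variance = (0.889/0.86 + 1.319)/82 = 0.0287; SE 0.169; power 85.4%.
- Adjusted information = 82 × (0.60 × 0.491 + 0.16 × 0.342 + 0.24 × 0.425) = 37.0; SE 0.164; power 87.4%.

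Simulation of this case gave 85.9% unadjusted, 86.7% with a before/after randomisation-date term, and 87.0% with the share-of-follow-up covariate. The formula gain of 2.0 points is thus somewhat optimistic; the simulated gain is 1.1.

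**Step 5: range** (same formulas, end-2022 boundary; power without → with the share-of-follow-up covariate).

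| Randomised in low period | 30% fall | 50% fall | 60% fall |
|---|---|---|---|
| 20% | 89.0 → 89.4 | 87.7 → 88.8 | 86.9 → 88.4 |
| 40% | 88.1 → 88.7 | 85.4 → 87.4 | 83.6 → 86.6 |
| 50% | 87.6 → 88.4 | 84.3 → 86.7 | 81.9 → 85.6 |

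A mid-2022 boundary gives smaller gains, down to about 0.3 points (89.2 → 89.5 at a 20% share and a 30% fall). A before/after randomisation-date term gains at most about 2.2 points over the same grid.

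**Step 6: what stays lost.** In the Step 4 case power falls 4.6 points from 90%. Even with the covariate it is 87.4% by formula or 87.0% in simulation, so 2.6 to 3.0 points of the shortfall remain.

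**The case against.** The strongest objection is that nothing here is an error. The treatment-only model is valid, the dispersion absorbs the heterogeneity, and extra covariates and pandemic sensitivity analyses commonly belong in the analysis plan, which the article promises. Much of this stands, and it is why the point is a recommendation about precision. It does not remove the point, because the article lists the terms of its primary model and separately reports the shift, without connecting the two.

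Three stronger readings are tempting, and the documents do not support them.

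- **Bias.** A reader might infer that changing incidence distorts the treatment effect. Randomisation is stratified by site in permuted blocks of 4–8, which keeps the arms roughly balanced over calendar time.
- **A large, avoidable loss.** Placing each participant wholly in one period gives gains of up to 7.6 points over falls of 20–60% and shares of 25–75%. Twelve-month follow-up straddles the boundary, which dilutes the contrast. Recruitment was also depressed in 2021–2022, which argues against a high share in the low period.
- **Changed ascertainment.** A reader might combine "undertaking online (telehealth) follow-up where possible and appropriate" with the child criterion "physician-confirmed acute change in respiratory rate, effort or chest signs" and infer under-counting in the restriction period. The article does not date the telehealth follow-up. Monthly contact by email, text or telephone was already the planned surveillance, supplemented by medical records. The physician-confirmed signs are only one of several alternative criteria. Nothing shows that detection changed, and the point does not rely on it.

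**Conclusion.** The point holds as a modest loss of precision. Neither the validity of the primary test nor the unbiasedness of the estimate is in question. Under the stated assumptions, a share-of-follow-up covariate gains about 0.3 to 4 power points, typically 1 to 2. The size of the fall, the share of follow-up affected and the dispersion are all missing from the article, so the actual gain could lie at the bottom of that range. The gain must not be presented as a cure for the low power that the article acknowledges, since fewer events cost power that no covariate returns. It is worth acting on because the change is nearly free and the article itself supplies the reason for it.

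**What to change.** Add one prespecified covariate to the primary negative binomial model: the proportion of each participant's planned 12-month window, counted from the randomisation date, that falls in the restriction period for that site or country. Use the planned window and not the observed follow-up, so that the covariate is fixed at randomisation and cannot be affected by treatment or withdrawal. Set the restriction dates before unblinding. Keep the months-in-study offset, and report the model without the covariate as a sensitivity analysis. A before/after randomisation-date indicator is simpler but recovers less.

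The cost is a sentence in the analysis plan, one extra parameter and the blind choice of dates. No participants, visits or new data are needed. If incidence had not fallen at all, the term would cost about half a power point (89.7% without and 89.2% with, in 600 simulated trials with half of participants in each period). Added after unblinding, it would have to be labelled an unplanned analysis under the article's own rule.
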